### Data and Outcomes

Data for research is collected by the lead researcher. This includes weekly extraction of data from OHP for those in the intervention arm in addition to questionnaire outlined below. For controls, photocopies of patients’ paper diaries are obtained when these patients attend their clinic appointments. In addition to these photocopies, where possible, BGL data are directly extracted from the BGL meter via USB cable connection. Finally, once patients have reached the study end point, they also asked to send outstanding self-monitoring data copies of their diaries via email or as photos via smartphone-based multimedia messaging service.

Demographic data together with diabetes self-efficacy and client satisfaction are collected at baseline with follow-up at least 6 weeks after enrollment in the trial. Self-efficacy and satisfaction are measured using the Diabetes Empowerment Scale–Short Form (DES-SF) [33] (Multimedia Appendix 3) and Client Satisfaction Questionnaire–8 Item (CSQ-8) [34,35] (Multimedia Appendix 4). The DES-SF is a shorter version of the original 28-item questionnaire for measuring self-efficacy in people with insulin- or noninsulin-treated diabetes [36]. The original questionnaire has three subscales: managing the psychosocial aspects of diabetes, assessing dissatisfaction and readiness to change, and setting and achieving goals. The longer version has high construct validity and good reliability [18,36]. The shorter version has 8 items, has high reliability (alpha of 0.85), and the scores were found to change positively with improvement in HbA_1c_ [33]. To minimize the burden on participating women we selected the DES-SF to assess diabetes self-efficacy. The CSQ-8 has been used in diabetes research [37] and was assessed for reliability and validity in a childbirth service evaluation [38]. It is reported to have strong reliability, excellent face validity [34,35], good psychometric properties, high client and staff acceptability, and sensitivity to programs of varying quality [37]. The CSQ-8 is available under paid license while the DES-SF is free with appropriate attribution. Both the DES-SF and SCQ-8 questionnaires are self-completed face-to-face or administered over the phone at baseline and at least six weeks from enrollment. Further information on outcomes and data collection time points is provided in Table 1.

The primary outcome of the quantitative exploratory RCT component of the study is service utilization. Maternal and fetal outcomes, satisfaction, and costs are secondary outcomes. In particular, one of the limitations of studies in our systematic review [11] was the lack of cost evaluation, however basic. Considering that studies appear to show virtually similar clinical outcomes between telemedicine and usual care/control [12,17-19], a form of cost comparison becomes important. There are several methods for undertaking health economic evaluation, one of which is cost minimization. This type of health economic evaluation is defined as “. . . evaluation method to use when the case for an intervention has been established and the programmes or procedures under consideration are expected to have the same, or similar, outcomes. In these circumstances, attention may focus on the cost side of the equation to identify the least costly option” [39]. At the time of this protocol study, patients not covered by the Australian Medicare paid AUD $280 for each face-to-face consultation with a clinician for GDM care at the centers in this study. Because diabetes education, endocrinology, and dietetics are the key outpatient specialties involved directly in GDM management and therefore targeted for influence by the TeleGDM intervention, the AUD $280 cost rate will be assigned to these for service provided to patients between study entry and study exit. Study participant outpatient consultations data covering service access between commencement of recruitment and end of data collection for computation of provider costs will be sourced from the hospital data management unit. While clinicians provide service over the phone, which is a cost to the hospital, patients are not billed and hence this cost will not be included. Furthermore, implementing the intervention required existing equipment and infrastructure for the brief induction. Costs for these were considered negligible and therefore were not taken into consideration. Also Australian public hospitals by their nature are nonprofitmaking entities. Where fees are charged these are normally break-even and include overheads. Besides the AUD $85 per patient subscription there is no separate license fee for OHP.

Technology is central to the telemedicine support service for GDM and an important feature for evaluation. As such, technology capability will be assessed through the volume of data uploads by patients and qualitatively through sections 2 and 3 (system and information quality) of the Health Infoway System and Use Assessment Survey [40] (Multimedia Appendix 5).

Outcomes of interest are outlined in Table 1. These are aligned with the dimensions of the telehealth evaluation framework proposed by the Institute for a Broadband-Enabled Society [41-43].

**Table 1 table1:** Outcomes and indicators matched to the telehealth evaluation framework dimensions.

	Outcome	Telehealth evaluation framework dimension	Measures/ indicators	Assessment instrument/ data source	Time point

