### Usual Care (Control)

Usual care refers to clinical GDM care processes currently in practice at the participating hospitals, and this will be the control group. In line with recommended best practice [29,30] diagnostic screening for GDM occurs at 24 to 28 weeks gestation for women with no known history of diabetes or earlier for those considered high risk for GDM. Following diagnosis through to end of pregnancy, ongoing care is provided via a multidisciplinary team of endocrinologists, dietitians, and CDE-RNs. The role of the team is in addition to obstetric care.

From an endocrinology perspective, care involves an initial group counseling and education with a CDE-RN and dietitian covering aspects of GDM self-management. The CDE-RNs provide the pregnant women with free BGL meters from an approved supplier. The meters are individual use and the women purchase their own consumables (ie, test strips and lancing devices). Treatment targets are ≤5.0 mmol/L for preprandial BGL and ≤6.7 mmol/L for 2-hour postprandial BGLs. Insulin is initiated or titrated if BGLs are above target over three successive days. Ongoing face-to-face appointments are scheduled with members of the team as needed until delivery. Appointments generally occur every one to two weeks as determined by the clinicians. Patients on insulin have more frequent reviews especially in the early stages of insulin initiation. Self-management involves keeping a daily paper diary record of GDM self-monitoring data (1 preprandial and 3 postprandial BGLs, insulin dosing, symptoms, and dietary information). The diaries are reviewed by the clinicians at each outpatient clinic. The women also have the option to call the CDE-RNs out of scheduled appointments if BGLs are outside target.

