**Figure 2 figure2:**
[figure not shown]
Diary view format introduced after modifications to enhance usability of OHP.

Upon enrollment, patient participants undergo individual semistructured 30 to 45 minutes induction by the lead researcher or research assistants.

The induction is hands-on and covers the initial set-up with participants practicing all the tasks they are expected to perform independently from then on. Induction covers signing up, logging on, navigating through the OHP Web portal, data entry, messaging, and reviewing data trend/summary graphs. All data entry is practiced using the previous day’s data. Performing BGL self-monitoring, administering insulin, and following dietary advice are part of routine diabetes education and counseling provided by a multidisciplinary endocrinology care team as described under usual care. Participants are also instructed on how to share this health information with the GDM clinicians for the purpose of providing clinical care and with the project lead investigator for research data collection and data management purposes. When required and in order to improve study data collection, the lead researcher may set up automatic reminders on OHP to send reminders every second day to prompt the noncomplying patient to enter data. Activating or setting up automated reminders is not routine but it is targeted for those who fail to perform data entry according to expectations. This avoids inundating those who are compliant with unnecessary reminders.

Participants are asked to enter their GDM self-monitoring data onto OHP daily or every other day in order to minimize backlogs and associated data entry errors. Maintaining a paper diary is optional. Automated alerts about new data entries are sent to the clinicians via email prompting the clinicians to log in under their credentials to review the patient data. When required and depending on the reviewed data or patient queries, clinicians provide feedback to the patient via the messaging service about any necessary alterations to treatment (eg, insulin titrations, changes to diet). The CDE-RNs act as the gatekeepers to interact with the telemedicine system and to consult or liaise with other GDM service team members. Patients can also email or print reports for other interested parties who do not have direct access to the Web-based shared data.

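### Blood glucose readings are collected by different routes in the two arms, so the secondary glycemic comparisons are open to differential measurement bias of unknown size and direction

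*Protocol article*

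**What the plan says.** Data and Outcomes describes BGL collection arm by arm. For the intervention arm it names "weekly extraction of data from OHP for those in the intervention arm". For the other arm: "For controls, photocopies of patients’ paper diaries are obtained when these patients attend their clinic appointments". The next sentence adds the device record: "In addition to these photocopies, where possible, BGL data are directly extracted from the BGL meter via USB cable connection". Because it refers back to those photocopies, its natural reading is that the meter download applies to controls. At study end, outstanding self-monitoring data are requested as diary copies.

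Telemedicine (Intervention) explains how readings reach OHP. The women enter them daily or every other day, "in order to minimize backlogs and associated data entry errors", and "Maintaining a paper diary is optional". Reminders go to women who do not enter data. No check of OHP entries against the meter is described.

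Table 1 gives OHP extraction, glucometer downloads and paper diaries as the sources for glycemic control, without arm or order of precedence. Under Usual Care, "The CDE-RNs provide the pregnant women with free BGL meters from an approved supplier", and the intervention is an adjunct to that care. Data Preparation and Analysis fills missing BGLs with the mean of nearby points and plans a survival analysis of time to glycemic stability.

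**The concern.** A between-arm difference in glycemia can be attributed to treatment only if glucose is ascertained in the same way in both arms. Here one arm has only self-entered values, while the other has self-written values plus a device record for some women. If hand-kept records lose readings in a way that depends on the value, the arm with more device data shows a different distribution even when true glucose is equal.

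Table 1 has no laboratory measure that could serve as a check, so glycemic control and time to stability rest entirely on these readings. They form part of the hypothesis that service use falls without compromising maternal and fetal outcomes, and the cost comparison is motivated by similar clinical outcomes. An artefact could create an apparent benefit, hide a worsening, or do the reverse. Readings never downloaded may also be impossible to recover at analysis.

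**Working it through.** The plan states no figure on this point, so there is none to reproduce. The check asks how large a difference the collection scheme could create when true glucose is identical in the two arms.

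**Inputs**
- From the document: the 2-hour postprandial target of 6.7 mmol/L (Usual Care) as cut-off; 100 women randomized 1:1, so 50 per arm.
- Assumed: true mean μ of 6.0 to 6.4 mmol/L and SD σ of 1.0 to 1.4; a fraction q of 10% to 30% of above-target readings omitted from hand-kept records; a fraction c of 0 to 1 of controls whose meter download replaces the diary.

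**Expected artefact**
- True share above target: p = 1 − Φ((6.7 − μ)/σ).
- Share in a hand-kept record: p_q = (1 − q)p / (1 − qp).
- With the same q in OHP and diary, telemedicine minus control = c(p_q − p). The mean shifts by c(p_q − p)(H − L), where H and L are the mean readings above and at or below 6.7.

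Upper end (μ = 6.4, σ = 1.4, q = 0.3): p = 0.415 and p_q = 0.7 × 0.415 / (1 − 0.3 × 0.415) = 0.332, a change of −8.3 points. H − L = 7.715 − 5.467 = 2.25, so the mean shifts by −0.083 × 2.25 = −0.19 mmol/L. These are the values at c = 1; at c = 0.5 they halve.

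Lower end (μ = 6.0, σ = 1.0, q = 0.1): p = 0.242 and p_q = 0.9 × 0.242 / (1 − 0.1 × 0.242) = 0.223, or −1.9 points and −0.03 mmol/L at c = 1.

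| Control meter coverage | Mean BGL artefact (mmol/L) | Share above target (points) |
|---|---|---|
| None | 0.00 | 0 |
| Half | −0.02 to −0.09 | −0.9 to −4.2 |
| All | −0.03 to −0.19 | −1.9 to −8.3 |

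**The sign is not fixed.** If diaries omit 30% of high readings and OHP 10%, the mean artefact is +0.07 to +0.13 with no meter data and +0.02 to +0.04 with half coverage. If 30% of in-target readings are left out of OHP and diaries are complete, it is +0.12 to +0.20. With complete entry it is zero.

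**False-positive rate.** Simulation under a true null: 50 women per arm, 200 readings each, mean 6.2, between-woman SD 0.6, within-woman SD 1.2, t-test on woman-level values, equal omission in OHP and diary. Ranges cover repeat runs.

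| Coverage | 10% omitted | 20% omitted | 30% omitted |
|---|---|---|---|
| None | about 5% | about 5% | about 5% |
| One quarter | about 6% | about 7% | about 9% |
| Half | 6–7% | 10–11% | 17–18% |
| All | 9–10% | 25–27% | 53–56% |

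These rates are for the share above target. On mean BGL, full coverage gives about 5–7%, 11–12% and 21–22%; half coverage gives about 6%, 7% and 8%.

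**Imputation.** With a true mean of 6.00, SD 1.2 and 30% of high readings omitted, the recorded mean is 5.86. After filling from the four nearest recorded points it is still 5.86, so the planned imputation does not remove the artefact.

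**The case against.** A reader might infer that controls are read from the meter while intervention women report what they choose, so that the comparison favours telemedicine. The document does not support this. The first control source is also hand-kept, and the meter is added only when feasible. Nothing says that it overrides the diary. Table 1 does not confine downloads to controls. The remark about data entry errors concerns backlogs and says nothing of selective omission. Clinicians review control diaries too, so awareness of being observed is not peculiar to one arm. All of this stands, and it removes any claim about direction.

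The size is also open. The highest rates need full control coverage, which the plan does not promise. The model applies the postprandial cut-off to every reading, although one of the four daily readings is preprandial with its own target. This stands too, so the figures are illustrative.

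Further, these are secondary outcomes in an exploratory trial. Birth size, ultrasound macrosomia, nursery admission and type of delivery do not use these readings. That limits the importance without removing the point.

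Finally, precedence among sources may be set out in a fuller document. That is fair for the precedence rule. It does not answer the collection procedure stated here: an analysis plan could restrict both arms to hand-kept values, but it could not supply intervention meter data that were never taken.

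**Conclusion.** The point holds as a risk of differential measurement, with unknown size and direction, for glycemic control and time to glycemic stability. It rests on the natural reading of Data and Outcomes, where the download is described only for controls. A bias towards telemedicine is plausible if high readings are under-entered in OHP and control meter data displace diaries; the document establishes neither, and other patterns reverse the sign.

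Under the stated assumptions the consequence runs from none (no control meter data, equal recording in both arms) to a false-positive rate above one half (full coverage, 30% of high readings omitted). Control meter coverage and the omission rate drive the result, and the plan gives neither. The primary service-utilization comparison is unaffected. This is worth correcting, but it does not undermine the trial.

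**What to change.** Download meters in both arms on the same basis, at clinic attendances and again at study end. The study-end download matters because the intervention is meant to reduce visits, and visit-based downloads alone could leave the telemedicine arm with lower coverage.

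Name one source type for the between-arm comparison: meter data in both arms, or patient-recorded data in both (OHP against diary), with the other as a sensitivity analysis. Meter data in both arms are preferable where coverage allows, because OHP and diary may still differ in what gets recorded. Do not fill gaps in one source from the other in a way that differs by arm.

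Recruitment was already underway when the article was submitted. For women past the point of download, compare patient-recorded values in both arms and use the control meter data only for validation. Report completeness and meter coverage by arm.

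The cost is a few minutes per woman, using meters that the clinics supply and a method already in use for controls. The downside is that coverage may stay incomplete.

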### Sample Size

As an exploratory RCT, a stringent sample size calculation was deemed to be less critical for the TeleGDM trial. Therefore sample size has been set at 100 participants. This determination was largely pragmatic, based on resources, time constraints, the balance of probability for detecting a statistically significant difference in the primary outcome and a reasonable power for secondary outcomes. Estimations based on a finding of 44% fewer clinic visits among those receiving telemedicine versus controls [32] indicated a required sample size of 42 with a power of 0.9 for a similar outcome. Thus if the primary outcome in our study were to be less than the latter cited study, or there was 30% attrition, our set target sample offers good prospects for detecting a difference in the primary outcome.

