**Primary**					
	Patient service utilization	Patient control	Number of scheduled face-to-face consultations	Attendances and nonattendances from outpatient activity dataset; patient medical records	Study exit
			Number of unscheduled face-to-face consultations		
			Number of telephone consultations		

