### Data Preparation and Analysis

Quantitative data analysis will be performed using Stata/IC 13.1 (StataCorp LP) with an intention to treat analysis. Missing data for the primary outcome is expected to be minimal as all patient appointments and outcomes are recorded. For the DES and CSQ-8 losses to follow-up will employ last observation carried forward for missing values. Since case BGL data is serial and expected to be nonlinear, case mean of nearby data points imputation will be used for missing data.

Summary univariate statistics will be used to describe the study populations and compare study groups at baseline. Categorical variables will be summarized as raw numbers and percentages and between groups comparisons will utilize chi-square statistics. Multivariate statistical analysis will be performed to compare the groups on primary and secondary outcomes. In addition, survival analysis will be performed to explore time to reach glycemic stability. Statistics will be reported with standard deviations or 95% confidence intervals as appropriate. Statistical significance will be indicated by *P*<.05.

Patient and clinician interviews will undergo thematic analysis supported by NVivo 11 (QSR International). The interview transcripts will be analyzed separately for each participant group using an inductive approach to identify and/or infer themes and codes from the transcripts. Further themes will be classified according to the dimensions of telehealth evaluation framework [41].

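### The one declared primary outcome, service utilization, is fixed as three unranked counts, and the sample size rests on clinic visits, which match none of them exactly

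*Protocol article*

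**What the plan says.** The Data and Outcomes section of the protocol article declares one primary outcome: "The primary outcome of the quantitative exploratory RCT component of the study is service utilization". That is a domain, not a variable. The variables stand in Table 1 under Primary, as three indicators of equal rank: "Number of scheduled face-to-face consultations", "Number of unscheduled face-to-face consultations" and "Number of telephone consultations". Their sources are the outpatient activity dataset, which covers both kept and missed appointments, and the medical records. The time point is study exit. Nothing marks one count as leading or says how the three are to be combined.

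The Sample Size section speaks of the primary outcome in the singular. It takes its effect from a cited study that found "44% fewer clinic visits among those receiving telemedicine versus controls". From this it derives a requirement of 42 at power 0.9, and the target is set at 100.

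Data Preparation and Analysis says: "Multivariate statistical analysis will be performed to compare the groups on primary and secondary outcomes". It gives one threshold for everything: "Statistical significance will be indicated by *P*<.05". It mentions no adjustment for several primary measures. The hypothesis at the end of the Introduction is that utilization will fall, without singling out a type of contact.

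**The concern.** A declared primary outcome should give one answer to one question. Here two things are left open.

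First, with three counts of equal standing and a general 5% threshold, the primary claim could rest on whichever count reaches significance. The error rate of that claim would then exceed 5%.

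Second, the three counts need not move together. The intervention shares monitoring data remotely and is expected to lead to fewer appointments, while women in usual care may telephone the diabetes educators between appointments. If face-to-face contacts fell and telephone contacts rose, or the reverse, the article gives no rule for saying whether utilization had decreased. This gap does not depend on any assumption about error rates.

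The sample size does not close it. The term clinic visits plainly leaves out telephone calls, but it does not say whether it means scheduled consultations, unscheduled ones or both.

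**Working it through.** **1. The plan's own figure.** The stated requirement is 42 for 44% fewer clinic visits at power 0.9. The article gives no control mean or standard deviation (SD) and does not say whether 42 is the total or per arm. The figure therefore cannot be reproduced, and it is not called wrong. What it implies, for a two-sided 5% comparison of two means with 1:1 allocation:

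- Standardised difference d = (1.960 + 1.282) × √(2/n per arm)
- 42 in total (21 per arm): d = 1.00, so SD / control mean = 0.44 / 1.00 = 0.44
- 42 per arm: d = 0.707, so SD / control mean = 0.44 / 0.707 = 0.62

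**2. The choice of count matters on the article's own figures.** The Introduction cites an earlier GDM telemedicine study with a separate P value for each of two counts:

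- face-to-face visits, 4.25 vs 6.22: 1 − 4.25/6.22 = 32% fewer
- unscheduled visits, 0.50 vs 2.89: 1 − 0.50/2.89 = 83% fewer

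Neither equals the 44% used for the sample size, which comes from a different cited study.

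**3. Error rate if the three counts are tested separately.** Inputs: three counts (Table 1) and α = 0.05 (Data Preparation and Analysis). Two-sided testing is assumed, as sidedness is not stated.

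- Independent tests, either direction: 1 − 0.95³ = 0.143, against 0.05
- Independent tests, favourable direction only: 1 − 0.975³ = 0.073, against 0.025

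The article gives no correlations between the counts, so these are assumed. A simulation of three equally correlated normal test statistics (1,000,000 draws) gives:

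| Assumed correlation | At least one significant, either direction | At least one significant, favourable direction |
|---|---|---|
| 0.3 | 13.6% | 6.8% |
| 0.5 | 12.5% | 6.3% |
| 0.7 | 10.9% | 5.5% |
| 0.9 | 8.4% | 4.2% |

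Every entry exceeds its single-test rate (5% and 2.5%).

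**4. Price of the alternative, adjusting for three tests.** Bonferroni uses 0.05/3 = 0.0167 per test. If the tests are independent, the overall rate is 1 − (1 − 0.0167)³ = 4.9%. At the effect implied by the stated 42:

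- power at 42 falls from 0.90 to 0.80
- restoring 0.90 takes 54 in total (if 42 is the total) or 54 per arm (if 42 is per arm)
- power with all 100 is 0.995 or 0.87 respectively
- power with 70 completers (100 less 30% attrition) is 0.96 or 0.71

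Naming one lead measure keeps the 5% rate with no such loss.

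**The case against.** **The trial is exploratory.** The article says so repeatedly and calls a stringent sample size calculation less critical. This stands as a reason to lower the importance. It does not remove the point: the article still declares a primary outcome, a directional hypothesis and a significance threshold, and it justifies its size partly by the chance of a significant primary result.

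**The analysis plan may settle it.** The model, the testing order and any adjustment may properly be fixed in a document not shown, and the planned multivariate analysis might mean one joint test. That is fair, and their absence here is not a fault. But which variable is primary is something the protocol itself defines, and Table 1 defines it as three unranked counts. A significant joint test would also not say whether utilization had gone down.

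**The text points towards face-to-face visits.** The sample size basis, the expected mechanism of fewer appointments, the link between cost savings and clinic attendance, and the Discussion's example of reduced utilization all do so. These are good grounds for choosing that measure. They do not designate it, and they leave scheduled versus unscheduled open.

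**No rise in telephone calls is predicted.** This is correct. The channel the intervention adds is portal messaging and SMS, and telephone calls belong to usual care, so they could fall as easily as rise. The point is only that opposite movements have no verdict, not that they are expected. Portal messages appear in none of the three counts.

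**Conclusion.** The point holds, with moderate importance. The primary outcome is fixed in a form that yields neither a single test nor a verdict when the counts diverge, and the sample size basis matches no row of Table 1 exactly.

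If the counts are tested separately at 5%, the chance of at least one false-positive primary result is 14.3% under independence and about 8% to 14% over assumed correlations of 0.9 to 0.3. In the favourable direction alone it is 7.3% against 2.5% under independence. These figures assume two-sided tests and, beyond independence, correlations that the article does not supply.

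A reader might infer more than the documents support:

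- That the plan commits to reading each count at 5%, so that any one makes the trial positive. The article states one general threshold; separate testing is implied, not stated.
- That 14.3% is the chance of a false claim of benefit. It includes significant increases in utilization and assumes independence.
- That the sample size already defines the lead measure. It names clinic visits only, and says nothing about attendance, the scheduled/unscheduled split, specialties or time window.

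**What to change.** Before analysis, which the article reports as still pending:

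- Name one primary measure, for example total attended face-to-face consultations (scheduled plus unscheduled) from study entry to study exit. It is the closest match to the basis of the sample size, though that section does not define it. Specifying attended consultations also settles how missed appointments in the data source are treated.
- Make the scheduled/unscheduled split and telephone consultations key secondary outcomes, reported next to the primary result.
- Word the primary conclusion as a change in face-to-face visits, not in overall service utilization, unless the other contact counts do not rise. Without this wording, a shift to other channels would count as success by definition.

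The cost is a sentence or two in the plan, with no new data and no loss of power relative to a single 5% test. The downside is that telephone or unscheduled counts alone can no longer carry the primary claim. If all three counts must stay primary, prespecify an adjustment and a rule for opposing movements, and accept the power loss shown in the working.
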